**Part-A**

**Title: “Virucidal Effect of Povidone Iodine on COVID-19 in Vivo: an open label randomized clinical trial"**

**Short title:** **Virucidal Effect of Povidone Iodine on COVID-19 in Vivo**

**Acronym: VEP-COV**

**Background:** It is an established fact that coronavirus spreads through respiratory droplets. Colonization of the virus in the oropharynx and/or nasopharynx is considered to be a major factor for transmissibility of the virus through respiratory secretions. Preventing colonization of the virus by administrating povidone iodine in the nasal passage is therefore a rational thought that is supported by recent evidence of the in vitro virucidal action of povidone iodine in severe acute respiratory syndrome coronavirus 2 (SARS CoV-2). Therefore, this study was designed to assess the virucidal effect of povidone iodine on the COVID-19 virus in vivo.

**Patients and Methods:** This open-label randomized clinical trial will be conducted at the Department of Otorhinolaryngology and Head Neck Surgery in collaboration with the Department of Virology and Department of Medicine in Dhaka Medical College Hospital (DMCH). The study will be conducted from September 2020 to December 2020. A total of 189 confirmed cases of COVID-19 disease proven by reverse transcription polymerase chain reaction (RT-PCR) testing will be enrolled in this study. Written informed consent will be ensured before participation. In case of no literacy, fingerprint will be considered for written permission. Consent will be sought from the legal guardian in case of minor or underaged. Formal ethical clearance will be obtained from the Ethical Review Committee (ERC) of Dhaka Medical College (DMC). All of the participants will be divided into seven Arms: Arm 1 will receive povidone iodine (PVP-I) nasal irrigation at a concentration of 0.4%, Arm 2 and Arm 3 will receive 0.5% and 0.6%, Arm 4 will receive PVP-I nasal spray at a concentration of 0.5% and Arm 5 will receive 0.6%. Arm 6 (placebo comparator group) will receive nasal irrigation with distilled water (DW), and Arm 7 (placebo comparator group) will receive nasal spray with distilled water. The contact time will be minimum 30 seconds. After the individual application of PVP-I and distilled water in the respective participants, they will be tested again for RT-PCR for COVID-19 from nasopharyngeal samples. All patients will be subjected to a detailed history, physical examination and adverse events. Computer generated randomization sequence will be followed for randomization. Data will be recorded in a semi structured questionnaire and will be analyzed by ‘R-4.0.2’ data analysis software.

**Conclusion:** It is expected that the study will reveal the virucidal activity with optimal contact time and concentration of nasal preparations of PVP-I against COVID-19. The results may help in prevention strategies for the general population, health care workers and COVID-19-positive patients.

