**Secondary objectives:**

1. To determine the efficacy of povidone iodine in clearing COVID-19 virus located in the nasopharynx
2. To assess the adverse events among the groups

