**Sample size:**

- - For 80% power, Z_β_=.84
  - For 0.05 significance level, Z_α_=1.96
  - r=1 (equal number of cases and control)
  - σ=10.0
  - Difference = 5.0

Therefore, n=126

Including exclusion criteria total sample 63*2+

30*2=186.

Therefore, in each group, a total of 27 samples will be collected after randomization.

**Number of participants:** The total number of participants will be 27 in each arm (7 Arm x 27=a total of 189 sample).

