**Procedure of randomization:** The study participants will be randomly assigned in this study into seven (7) equal Arm, where each arm has equal opportunity to receive any treatment option. Randomization will be performed by computer generated random sequences.

- - Arm 1 will receive povidone iodine (PVP-I) nasal irrigation at a concentration of 0.4%
  - Arm 2 will receive povidone iodine (PVP-I) nasal irrigation at a concentration of 0.5%
  - Arm 3 will receive povidone iodine (PVP-I) nasal irrigation at a concentration of 0.6%
  - Arm 4 will receive PVP-I nasal spray at a concentration of 0.5% with standard care.
  - Arm 5 will receive PVP-I nasal spray at a concentration of 0.6%
  - Arm 6 (placebo comparator group) will receive nasal irrigation with distilled water
  - Arm 7 (placebo comparator group) will receive nasal spray with distilled water

This can be done quickly, with baseline information typically captured in <15 min. Recruitment & randomization will be performed contemporaneously with assessment/resuscitation of patients by a second person so that medical care is not delayed by recruitment. Patients will only be randomized once baseline data have been entered; after this has been done, participants will not be withdrawn from the study. Following tossing, the trial physicians reported the principal investigator (PI) of the trial, and then the PI handed over an opaque sealed envelope, which will be numbered sequentially to correspond to patient enrolment numbers, which will be used for concealment of treatment allocations. Envelopes will be kept in a locked drawer and will be opened in strict numerical order by supervisor in the presence of the nursing supervisor of the study unit. Allocation between arms will initially be equal, although this may be revised following guidance of the PI and his team (as per the statistical plan).

**Withdrawal of study participants:** Participants are free to withdraw from the study at any point, for any reason. If this occurs, the primary reason for withdrawal will be documented in the participant’s case record form. The participant will have the option of withdrawal from:

- Study medication with continued study procedures and collection of clinical and safety data,
- All aspects of the trial but continued use of data collected up to that point,
- All aspects of the trial with the removal of all previously collected data, or

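### The protocol's summary expects an optimal contact time and concentration, but contact time is not varied and arms of 27 cannot reliably separate 0.4%, 0.5% and 0.6%

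*Protocol*

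**What the plan says.** The Conclusion in Part-A of the protocol states: "It is expected that the study will reveal the virucidal activity with optimal contact time and concentration of nasal preparations of PVP-I against COVID-19". It adds that the results may help prevention in the public, health care workers and patients.

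The rest of the protocol is narrower:

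- **Hypotheses and objectives.** The hypotheses ask whether nasal PVP-I clears virus from the nasopharynx. The general objective is virucidal efficacy there. The secondary objectives are "To determine the efficacy of povidone iodine in clearing COVID-19 virus located in the nasopharynx" and adverse events among the groups.
- **Arms.** Under Procedure of randomization, irrigation is given at 0.4%, 0.5% and 0.6% (Arms 1 to 3) and spray at 0.5% and 0.6% (Arms 4 and 5). Each route has its own distilled-water control (Arms 6 and 7).
- **Contact time.** A minimum of 30 seconds is given for the active arms, and the controls have the same duration. The Dosing regimen describes administration over 2 minutes, again the same for controls. No arm is assigned a different time.
- **Size.** Under Sample size, a two-group calculation (SD 10, difference 5, 80% power, 0.05) gives 126. Sixty more are added to make 186, and then: "The total number of participants will be 27 in each arm (7 Arm x 27=a total of 189 sample".
- **Analysis.** Chi-square, t test or ANOVA, each judged at P < 0.05.

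**The concern.** The summary attributes to the trial a result that the objectives do not seek and the arms were not sized to give. An optimum requires comparing levels of a factor. Contact time has one specification for all arms, so it has no levels to compare. Concentration has levels 0.1 points apart, and no step of the sample-size reasoning concerns differences between them.

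At stake is how the results are read. With small arms, observed clearance will usually differ visibly between concentrations even if the true rates are equal. A summary that already expects an optimum invites the reader to treat that spread as a finding. This is distinct from multiplicity against control: it remains even if every active arm truly beats its control. In addition, a statement about nasal preparations in general cannot cover 0.4%, which has no spray arm.

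**Working it through.** **Inputs from the protocol.** SD 10, difference 5, z values 1.96 and 0.84, 27 per arm, three irrigation and two spray concentrations. The units of SD and difference are not stated. The protocol gives no clearance rates, so all rates below are assumptions, shown over a range.

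**1. The protocol's own figure.** n per group = 2 × [SD × (1.96 + 0.84) / difference]² = 2 × (10 × 2.8 / 5)² = 62.7, rounded to 63. Two groups make 126, as stated. Then 63 × 2 + 30 × 2 = 186; 186 / 7 = 26.6, rounded to 27; 7 × 27 = 189.

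**2. One pair of arms on that scale.** The standard error of a difference is 10 × √(2/27) = 2.72.

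- Power for a difference of 5: Φ(5/2.72 − 1.96) = Φ(−0.12) = 45%.
- Difference detectable with 80% power: 2.8 × 2.72 = 7.6.
- Half-width of the 95% interval: 1.96 × 2.72 = 5.3, wider than the design difference itself.

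**3. One pair of arms on binary clearance.** For 70% against 80%, the standard error is √[2 × 0.75 × 0.25 / 27] = 0.118 under the null and √[(0.70 × 0.30 + 0.80 × 0.20) / 27] = 0.117 under the alternative. Power is about Φ[(0.10 − 1.96 × 0.118) / 0.117] = Φ(−1.12) = 13%. Exact enumeration of the uncorrected chi-square test gives 14.6%. For other 10-point differences, from 50% v 60% to 80% v 90%, the normal approximation gives 11% to 17%. With 70% in both arms, the half-width of the interval for the difference is 1.96 × √(2 × 0.7 × 0.3 / 27) = 24 points.

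**4. Ranking the irrigation arms if they are truly equal.** Simulation of 400,000 trials, three independent Binomial(27, p) counts:

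| True clearance, all three arms | Mean best-to-worst gap | Gap of 10 points or more |
|---|---|---|
| 70% | 15 points | 74% |
| 80% | 13 points | 67% |
| 90% | 10 points | 48% |

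With ties split, each arm leads in one third of trials.

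**5. Ranking if there is a true gradient.** Same simulation, ties for first place split equally:

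| True clearance at 0.4 / 0.5 / 0.6% (assumed) | Truly best arm leads |
|---|---|
| 70 / 75 / 80% | 59% |
| 60 / 70 / 80% | 78% |
| 50 / 70 / 90% | 97% |

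The rising direction is only for illustration; a falling gradient gives the same figures by symmetry of the labels.

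**6. The written significance rule applied to equal arms.** With three equal irrigation arms at 70% or 80%, the overall chi-square is significant at 0.05 in about 5% of trials. At least one of the three unadjusted pairwise tests is significant in about 13%.

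**7. Contact time.** No arithmetic applies. All arms share one minimum, and times above it would vary by circumstance and not by randomisation. A comparison of longer with shorter contact would be observational.

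**The case against.** The sentence is an expectation in a summary. It is not an objective, and nothing in the hypotheses or objectives commits the trial to choosing a concentration. That is correct, and it limits the defect to a claim that outruns the design.

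A reader might go further and infer that the arm with the highest observed clearance will be reported as optimal, so that chance would produce a winner in most trials. The protocol does not say so. Its only written rule is P < 0.05, and under that rule equal arms would seldom yield a significant difference (step 6). The gaps in step 4 show how unreliable a ranking would be; they are not the rate of false claims under the plan.

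Three other readings also go too far:

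- **The missing definition of an optimum is itself an error.** How arms are compared may be set out in a statistical analysis plan that is not shown; the randomisation section refers to a statistical plan.
- **Irrigation and spray will be pooled.** They are separate arms with separate controls, and nothing says that they will be combined.
- **The trial cannot rank concentrations at all.** If each step were worth 20 points, the ranking would be right about 97% of the time.

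What stands is that no analysis plan can supply variation in contact time, a 0.4% spray arm, or more than 27 patients per arm.

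**Conclusion.** The point holds as a mismatch between the summary and the design. For contact time it is certain and needs no assumption. For concentration it rests on precision: about 15% power for 70% against 80% clearance, and about 45% for the protocol's own difference and SD. The latter should not be read as a broken promise of 80% power between concentrations, because the protocol's calculation is for two groups and does not mention concentrations. It is also illustrative, since the units are not given.

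How often a ranking would mislead cannot be fixed from the document. It ranges from a purely random order if the concentrations are equally effective to about 3% wrong for a very steep gradient. The protocol gives no reason to assume steepness. The correction is worth making because it costs only wording, but it does not undermine the comparisons with control that the objectives describe.

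**What to change.** In the Part-A Conclusion, delete the expectation of an optimal contact time and concentration. Suggested replacement: *The study will report clearance and adverse events at each concentration against the route-matched control, with 95% confidence intervals; no optimal concentration or contact time will be claimed from ranking the arms.*

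In the Proposed Analysis Plan, add that any comparison between concentrations is made within route, is labelled exploratory and is reported with its interval. State that 0.4% is not studied as a spray. A rule that names a preferred concentration from a linear slope is best avoided: a slope can favour only an end of the range, never 0.5%.

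The cost is wording in two sections and a less favourable stated conclusion. No extra patients are needed. If the sponsor does want to select a concentration, the arms must be sized for it. On the protocol's scale, with 80% power, two-sided 0.05 and no adjustment, a gap of 5 between adjacent concentrations needs 63 per arm, and a gap of 2.5 needs 252.

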**Part-B**

**Title: “Virucidal Effect of Povidone Iodine on COVID-19 in Vivo: an open label randomized clinical trial"**

**Introduction**

Severe acute respiratory syndrome coronavirus 2 (SARS-CoV-2) has emerged as a new pathogen of the coronavirus family responsible for the coronavirus disease 2019 (COVID19) pandemic. The number of infections has grown exponentially over a short period of time (Pelletier *et al.*, 2020; Zhao *et al.*, 2020). Within seven months of its emergence in December 2019, the virus has spread rapidly and infected at least 12 million people worldwide, causing over half a million deaths from the disease (WHO, 2020). SARS‐CoV‐2 is an enveloped, positive-sense, single-stranded RNA virus and belongs to the same class of beta-coronaviruses as SARS-CoV and MERS-CoV, the viruses responsible for the Severe Acute Respiratory Syndrome (SARS) 2003 and Middle East Respiratory Syndrome (MERS) 2012 epidemics, respectively (Anderson *et al.*, 2020; Zhu *et al.*, 2020). Current evidence indicates that human-to-human transmission primarily occurs through respiratory droplets from coughs or sneezes and/or physical contact. As the virus can persist on contaminated surfaces for days, infection can occur indirectly by touch transfer of virus from these surfaces or hands to the mucosa of the mouth, nose or eyes (Anderson *et al.*, 2020; Chin *et al.*, 2020).

Viral loads are high in the nasal cavity, nasopharynx and oropharynx. Nasal goblet and ciliated cells within the respiratory epithelium have the highest expression of angiotensin converting enzyme 2 (ACE 2), the main receptor of COVID-19. Multiple reports have demonstrated that the nasal cavity, nasopharynx and oropharynx are important routes of transmission. Aerosol-generating procedures can enhance this transmission via transit through these areas of high viral content, releasing aerosols that can remain in the air for up to 3 hours. Transmission can occur in subclinical asymptomatic carriers, symptomatic infected carriers and convalescent seroconverted patients (Doremalen *et al.*, 2020; Pelletier *et al.*, 2020; Zou *et al.*, 2020). There is a growing need to develop processes to reduce virus transmission, as standard precautions, including the donning of masks and gloves, may not be sufficient. Early experience with COVID-19 outbreaks in hospital and healthcare settings has led frontline providers to suggest nasal and oral application of PVP-I as part of a transmission reduction plan (Mady *et al.*, 2020).

Povidone-iodine (polyvinylpyrrolidone iodine, PVP-I) is a water-soluble complex of povidone, a carrier molecule, and iodine that has powerful microbicidal activity. PVP-I formulations have been widely used for >60 years because of their broad-spectrum antimicrobial activity and established safety profile (Anderson *et al.*, 2020). It is available in various preparations for use as a disinfectant for skin, hand and mucosal surfaces, as well as for wound treatment and eye applications (Eggers *et al.*, 2018). The antimicrobial action of PVP-I occurs after free iodine dissociates from the polymer complex. Once in the free form, iodine rapidly penetrates microbes, disrupts proteins and oxidizes nucleic acid structures. This interaction ultimately results in microbial death (Kirk-Bayley *et al.*, 2020).

Interest in the use of PVP-I against coronaviruses was first reported in response to the SARS and MERS outbreaks in the past decade. Commercially available 10% PVP-I solutions have been tested against human coronaviruses HCoV 229E, HCV0OC43, SARS and MERS18, although these commercial solutions are unsuitable for use in the nasal and oral cavities at commercially available concentrations. Homology with the current COVID-19 pathogen suggests that PVP-I might be effective, but there are no reported studies that have concluded the efficacy against SARS-CoV-2 for any PVP-I solutions (Pelletier *et al.*, 2020). Therefore, the purpose of the randomized clinical trial is to investigate the virucidal activity of povidone iodine on COVID-19 located on the mucosal surface of the oral cavity, oropharynx and nasopharynx among COVID-19-positive patients seeking health care from Dhaka Medical College Hospital.

**Rationale of the study**

Coronavirus disease 2019 (COVID-19) is a highly infectious disease that causes human-to-human transmission primarily by respiratory droplets from coughing, sneezing and speaking. In early SARS-CoV-2 infection, a greater viral titre can be found in saliva and nasal mucous; minimization of these titres should help to reduce cross infection. Povidone-iodine (PVP-I) disinfectant has better antiviral activity than other antiseptics and has already been proven to be an extremely effective virucide in vitro against severe acute respiratory syndrome and Middle East respiratory syndrome coronaviruses (SARS-CoV and MERS-CoV). Its in vivo virucidal activity is unknown, although its nasal or oral preparation can be effective in reducing transmission. Earlier, very few studies evaluated the efficacy of povidone-iodine as a nasal antiseptic or oral rinse antiseptic against the SARS-CoV-2 virus, but the results of those studies are not undebatable. Therefore, the aim of this study was to investigate the virucidal activity of povidone iodine on coronaviruses located on the mucosal surface of the oropharynx and nasopharynx, which is very rational in this pandemic period.

**Research Hypothesis:**

**Null hypothesis:** Administration of nasal preparations of povidone-iodine (PVP-I) is no longer effective in clearing COVID-19 virus located on the mucosal surface of the nasopharynx.

**Alternative Hypothesis:** Nasal preparations of povidone-iodine (PVP-I) can effectively clear COVID-19 virus located on the mucosal surface of the nasopharynx.

**Objectives:**

**General Objective:**

To determine the virucidal efficacy of povidone iodine on COVID-19 virus located in nasopharynx.

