**Dosing regimen:**

**Intervention Arms (Arms 1, 2, 3, 4, 5):** Participants allocated to PVP-I solution (especially prepared for the study) after confirmation of COVID-19 positivity. Proper dilution with normal saline will be added, which will be physically and chemically stable for 6 hours. Other supporting care (crystalloid solution infusion), and monitoring of vital statistics, in case of bleeding protective measures will be performed according to the national guidelines.

**Control Arms (Arms 6 and 7):** Participants allocated distilled water for nasal irrigation for Arm 6 a placebo that will also be reconstituted and applied at the same rate as mentioned in the invention groups and distilled water for nasal spray for Arm 7 a placebo that will also be reconstituted and applied at the same rate as mentioned in the invention groups.

In both Arms of patients, 10 ml of PVP-I or distilled water will be administered for 2 minutes. Nasal spray will be administered in each nostril using an atomizing device (2 sprays for average device). Control groups, will receive distilled water irrigation and distilled water nasal spray at similar amounts and durations. Further RT-PCR will be assessed within 1 minutes to 15 minutes of the following intervention.

**Participant compliance:** The study team will not create any problem with compliance while the patient is under care and supervision in the hospital. It will be ensured that all recruited patients will receive the appropriate interventions, although they could be interrupted due to the onset of potential adverse effects such as hypotension.

**Overdose:** The study team will titrate the drugs against the key adverse effect of hypotension. Nasal spray and nasal irrigation will be halted if patients complain of significant discomfort or clinically significant hypotension or signs of anaphylaxis. Procedures will be started again at a lower rate if the condition settles or according to the patient’s choice.

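### The stated aim is virucidal efficacy, but the only efficacy measurement is an RT-PCR within 15 minutes, which detects RNA and cannot show that virus was inactivated

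*Protocol*

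**What the plan says.** The Protocol uses two different terms for what povidone iodine is meant to do.

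- **Virucidal.** The General Objective is "To determine the virucidal efficacy of povidone iodine on COVID-19 virus located in nasopharynx". The title, the Part-A Background and the Rationale use the same term. The Part-A Conclusion states: "It is expected that the study will reveal the virucidal activity with optimal contact time and concentration".
- **Clearing.** The first secondary objective is listed separately: "To determine the efficacy of povidone iodine in clearing COVID-19 virus located in the nasopharynx". The alternative hypothesis says that nasal preparations "can effectively clear COVID-19 virus located on the mucosal surface of the nasopharynx", and the Proposed Analysis Plan also states its aim as clearing.

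One efficacy measurement serves both. Under Patients and Methods, after application "they will be tested again for RT-PCR for COVID-19 from nasopharyngeal samples". Under Dosing regimen, "Further RT-PCR will be assessed within 1 minutes to 15 minutes of the following intervention". Follow-up lasts 2 days or until discharge criteria are met, but no later RT-PCR is described, and neither is a culture or any other test of infectivity. The second secondary objective concerns safety: "To assess the adverse events among the groups".

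On mechanism, the Introduction says that free iodine "iodine rapidly penetrates microbes, disrupts proteins and oxidizes nucleic acid structures".

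**The concern.** A virucidal claim is a claim about infectivity. RT-PCR reports whether viral RNA was detected in the sample. Because the Protocol lists virucidal efficacy and clearing as separate objectives, the first cannot simply be read as another name for the second.

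The mismatch can mislead in either direction:

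- Virus inactivated through protein damage, one of the mechanisms the Introduction names, may still carry detectable RNA. A null result would not refute virucidal action.
- Iodine still on the mucosa or swab might reduce detection by acting on RNA or on the reaction, with no change in infectivity. The sample may be taken as early as one minute after application. Only Arms 1-5 carry iodine, so comparison with water does not cancel this, and the error would favour povidone iodine.

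Part-A says that the results may inform prevention for the general population, health care workers and patients. If the plan is followed exactly, a difference from water would be reported to those readers as in vivo virucidal activity, which the data cannot show.

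**Working it through.** **1. Claims against measurement**

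| Statement | Where | Served by RT-PCR at 1 to 15 minutes? |
| --- | --- | --- |
| Virucidal efficacy | Title, General Objective, Part-A Conclusion | No. RNA detection does not measure infectivity. |
| Clearing virus from the nasopharynx | Research Hypothesis, Secondary objectives, Proposed Analysis Plan | Yes, if clearing is defined as no detectable RNA at that time. |
| Adverse events | Secondary objectives | Not applicable; observed separately. |

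No analysis choice can recover infectivity from this assay, so the mismatch is not a detail that could be left to a later analysis plan.

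**2. What the water arms control**

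| Reason for a negative swab | Active arms | Water arms of the same route | Cancels in the comparison? |
| --- | --- | --- | --- |
| RNA rinsed away | Yes | Yes, at similar amounts and durations | Largely. The active product is diluted with normal saline and the controls are distilled water. |
| Chance negative on repeat test | Yes | Yes | Yes |
| Residual iodine lowering detection | Possible | No | No |

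**3. Source of the arm size**

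From the Sample size section: 2 × (10 × (1.96 + 0.84) / 5)² = 62.72, rounded up to 63 per group, or 126 in total. Then 63×2 + 30×2 = 186; 186/7 = 26.57, rounded up to 27; 7 × 27 = 189. These figures reproduce and are not at issue here. The formula is for a difference in means, so the Protocol does not itself fix a binary 27 v 27 comparison. The illustration below assumes one.

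**4. How much interference would matter (illustration)**

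Assume no effect on virus. Let *q* be the proportion of control swabs that are negative, and *f* the share of otherwise positive active-arm swabs that residual iodine turns negative. The active-arm negative rate is then *q* + (1 − *q*)*f*. For example, *q* = 0.05 and *f* = 0.20 give 0.05 + 0.95 × 0.20 = 0.24. The Protocol gives neither *q* nor *f*.

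The probability of a significant result favouring povidone iodine, by exact binomial enumeration at 27 v 27 with a two-sided chi-square test at 0.05, is:

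| Control negatives *q* | Test | *f* = 10% | *f* = 20% | *f* = 30% |
| --- | --- | --- | --- | --- |
| 5% | Uncorrected | 22% | 56% | 83% |
| 5% | Continuity-corrected | 6% | 32% | 67% |
| 10% | Uncorrected | 16% | 42% | 70% |
| 10% | Continuity-corrected | 6% | 25% | 54% |
| 20% | Uncorrected | 11% | 27% | 49% |

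With no interference the uncorrected figure is 1.2% at *q* = 5% and 2.6% at *q* = 10%. At *q* = 5% and *f* of 2% to 5%, it is 3% to 8%.

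The choice of test matters because expected counts are small. At *q* = 5% and *f* = 10%, the expected negatives per arm are 27 × (0.05 + 0.145)/2 = 2.6, and at *f* = 20% they are 27 × (0.05 + 0.24)/2 = 3.9. Both are below 5.

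**The case against.** The case on the other side has real force.

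- **Wash-off.** A reader might infer that the trial cannot separate killed virus from RNA rinsed away. The Protocol does not support that in full. Arms 6 and 7 are randomized, use the same two routes and apply similar amounts for similar durations, so a within-route comparison largely removes rinsing. What stands is the saline and distilled-water difference, and the fact that a before-and-after reading within one arm would not have this protection.
- **Outcomes.** RT-PCR is the only efficacy measurement, but not the only outcome, because adverse events are also assessed.
- **The hypotheses already say clear.** So do the first secondary objective and the analysis aim. RT-PCR against water is much closer to that wording, so the tested claim is better served than the title is. This narrows the rewording needed but leaves the General Objective out of line with the hypothesis.
- **Interference is unproven.** The Protocol has no data on it and does not name the assay. Laboratory controls are commonly set out in laboratory procedures, and the Department of Virology collaborates. Silence on kit-level checks is not an error. Nor is all RNA loss artefact: the Introduction presents nucleic acid oxidation as part of iodine's action. RT-PCR still cannot separate that action from interference.
- **The probabilities depend on assumptions.** They fall sharply with low interference, more control negatives or a continuity correction. They show what could happen and do not estimate what will.

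**Conclusion.** The point stands in a limited form. The virucidal claim in the title, General Objective and expected conclusion goes beyond what the efficacy measurement can show, whatever the result. This rests only on the Protocol's own text and on RT-PCR detecting RNA rather than infectivity; it needs no assumption about interference.

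Residual iodine is a second, possible source of error that would favour povidone iodine and that the water arms cannot remove. Its size is unknown. The illustrative chance of a false result ranges from 3% (2% interference, 5% control negatives, uncorrected) to 83% (30% interference, same conditions), and these figures should not be cited as a predicted error rate.

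A reader might go further and infer that the trial is uninformative, or that a positive result would be artefact. The Protocol supports neither. The randomized comparison with route-matched water can still support a narrower statement about short-term RT-PCR detectability, subject to the interference caveat.

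**What to change.** 1. Reword the title, the General Objective and the Part-A Conclusion to what is measured: the proportion of participants with no RT-PCR-detectable SARS-CoV-2 RNA in the nasopharynx within 15 minutes of application, compared with the distilled-water control of the same route.
2. Define clearing in exactly that way in the Research Hypothesis, the first secondary objective and the Proposed Analysis Plan. The word itself can stay.
3. Drop virucidal as a claim of the trial, including where the Part-A Background and the Rationale state the study's aim. It can remain where the text describes the in vitro evidence.
4. Optional: if the RT-PCR kit has an internal control, record its result for each sample and report by arm the negatives whose control failed. This would catch a failed reaction, but not viral RNA damaged on the mucosa or swab before the assay, so it is only a partial safeguard.

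Items 1 to 3 cost a wording amendment and a more modest claim. They leave the arms, number of participants, sampling and treatment unchanged. Item 4 adds one field to the laboratory form and depends on the kit, which the Protocol does not name.
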